#### 7.4.5 Secondary outcomes –Timing of subsequent epinephrine, pulse check and defibrillation

Timing of subsequent epinephrine, pulse check and defibrillation will be quantified as the deviation from the theoretic target intervals (theoretical epinephrine interval: every 4 minutes; and theoretical pulse check and defibrillation interval: every 2 minutes). Mixed effect linear regression models will be used to evaluate the effect of intervention on the absolute deviation from these theoretical value – treating early and delayed events equally (i.e., 10 seconds too early and 10 seconds too late are both considered 10-second deviation). To account for multiple measurements within the same simulation event, a random intercept for event will be included in the model. Model estimates will be reported as mean differences with corresponding 95%CI for all these outcomes.

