### 3.2 Orientation and Simulation Scenarios

Following randomization (1:1 ratio), all participants will view a standardized orientation video describing the clinical environment, equipment, manikin functionality, and participant roles. The intervention group will receive additional orientation to the InterFACE-AR system, comprised of (1) a 10-minute instructional video describing the system's components and functions; (2) a 5-minute hands-on training session using the assigned device (Guiding Pad app for medication nurse, AR headsets for team leader and medication nurse) and comprised of opportunity to use and practice their assigned task, guided by a checklist, and (3) a 4-minute verbal scripted walk-through scenario allowing participants to use the system in their assigned roles.

A 12-minute CA simulation scenario (pulseless electrical activity [4 minutes] → pulseless ventricular tachycardia [4 minutes] → ventricular fibrillation [4 minutes] → return of spontaneous circulation) will be run by both groups. Both recruitment sites will utilize the identical pediatric manikin (SimJunior™, Laerdal Corporation), specifically designed and calibrated for CPR training. All simulation scenarios will be tightly standardized by using a scenario template with highly scripted actor roles and patient progression. After the session, participants will be instructed not to disclose any information from the scenario to other participants to prevent any preparation bias.

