#### **7.4.6 Secondary outcomes - UEQ and TAM (for intervention group only)**

The User Experience Questionnaire (UEQ) and the Technology Acceptance Model (TAM) survey will be administered to participants in the InterFACE-AR group only. Rather than presenting data for each individual item, we will report the statistical summaries (mean and standard deviation) for each construct within both tools. The UEQ includes six constructs: attractiveness, perspicuity, efficiency, dependability, stimulation, and novelty. The TAM includes two constructs: perceived usefulness and perceived ease of use. For each construct, the mean and standard deviation will be reported, and Cronbach's alpha will be calculated to assess the internal consistency of the items within each construct.

In the case of missing data, a complete case analysis will be conducted. No multiple imputations are planned. All statistical tests will be two-sided with a type one error risk of 5%. All statistical analyses will be performed with R software (version 4.5.0; Foundation for Statistical Computing).

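### In 7.4.5, a due repeat dose, pulse check or shock that is omitted with no later event leaves no trace in the analysis, and no rule covers the open interval

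*Combined protocol and SAP*

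**What the plan says.** Section 7.4.5 defines the outcome: "Timing of subsequent epinephrine, pulse check and defibrillation will be quantified as the deviation from the theoretic target intervals". The targets are "theoretical epinephrine interval: every 4 minutes; and theoretical pulse check and defibrillation interval: every 2 minutes". The absolute deviation is analysed, "treating early and delayed events equally", in a mixed linear model. On repeated measurements it adds: "To account for multiple measurements within the same simulation event, a random intercept for event will be included in the model". The section gives no number of due events per scenario, no score for a due event that never happens, and no rule for an interval still open when the scenario ends.

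The general missing-data rule stands at the end of 7.4.6: "In the case of missing data, a complete case analysis will be conducted. No multiple imputations are planned". Section 3.2 fixes the observation window: "A 12-minute CA simulation scenario", made up of 4 minutes each of pulseless electrical activity, pulseless ventricular tachycardia and ventricular fibrillation.

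**The concern.** An interval needs two events. If a team stops giving epinephrine, checking the pulse or shocking, the last interval never closes and produces no observation. Failing to do a due step is a plain failure of adherence, which is the second scientific aim (2.3). The system's prompts for drugs and defibrillation (2.2) could be expected to prevent it.

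Whether an interval is observed depends on what the team did after randomisation. If teams in one arm stop early more often, the comparison is restricted to the events that were carried out. The arms can then look alike on timing while differing in how often due steps were left out. With 9 teams per arm and few intervals per team, a handful of such teams matters.

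**Working it through.** Section 7.4.5 states no numerical result to reproduce. The check is interval arithmetic on the plan's figures, followed by an illustration.

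**Inputs from the documents**
- Scenario length: 12 min = 720 s (3.2).
- Targets: 240 s for epinephrine, 120 s for pulse checks and shocks (7.4.5).
- Typical first epinephrine dose: 165 s (7.1). I count this from the start of the scenario.
- 9 teams per arm (7.1).

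**Formulas**
- Closed interval: deviation = |t(k+1) - t(k) - target|.
- Open interval: excess = end - t(last) - target, if positive.

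**Epinephrine, first dose at 165 s**

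| Doses given (s) | Planned deviations (s) | Open interval at 720 s | Excess over 240 s |
|---|---|---|---|
| 165, 405, 645 | 0, 0 | 75 | none |
| 165, 405 | 0 | 315 | 75 |
| 165 | no row | 555 | 315 |
| 165, 645 | 240 | 75 | none |

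Rows two and four each omit one dose. Omitting the last costs nothing; omitting the middle one costs |645 - 165 - 240| = 240 s. With on-target repeats only two intervals fit, because a third would end at 165 + 3 × 240 = 885 s, after the scenario is over. One lost interval is therefore half of a team's epinephrine data.

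**Shocks, assumed due at 250, 370, 490 and 610 s**
- All given: 0, 0, 0.
- Last omitted: 0, 0.
- Last two omitted: 0.
- Only the first given: no row.
- Second omitted, then resumed: 120, 0.

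**Illustration for epinephrine**

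Simulation of 4,000 trials with 9 v 9 teams. First dose: mean 165 s, SD 25.2 s (centred on the figures in 7.1). Later intervals: mean 240 s, SD 30 s in both arms. The SD of 30 s and the omission rates are assumptions; the documents give neither. A team that omits gives no further dose. The ranges cover omission drawn once per team or at each due dose. Differences are intervention minus control.

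| Omission, control v intervention | Planned rows | Open interval added, pooled rows | Open interval added, team means |
|---|---|---|---|
| 30% v 10% | about 0 s | about -38 to -43 s | about -58 to -63 s |
| 20% v 0% | about 0 s | about -34 to -39 s | about -58 to -63 s |
| equal | about 0 s | near 0 s | near 0 s |

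At 30% v 10%, 30% of control and 10% of intervention teams contribute no epinephrine interval. Pooled rows isolate the effect of adding the open interval. Team means also change the weighting, which accounts for about a third of the larger figure. Neither summary fits the planned mixed model.

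**Illustration for shocks**

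This assumes four due shocks, equal timing accuracy in both arms (SD 15 s within and 8 s between teams), and omission in 50% of control and 10% of intervention teams.
- Last shock omitted: the difference moves from about 0 s to about -13 s when the open interval is scored.
- Last two omitted: it moves from about 0 s to about -37 s.
- Middle shock skipped: it is about -18 s either way, because the planned outcome already counts that omission.
- Every shock after the first omitted: about 5.4 of 18 teams have no row.

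**The case against.** A reader might infer that any team omitting a due event is dropped or scored as perfect. The documents do not support that. A team that skips and resumes gets a long interval and a large penalty (240 s for epinephrine, 120 s for a shock or pulse check). A score of 0 s after early stopping is a consequence of the rows that remain; the text states no such rule.

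A reader might also infer that the analysis would favour the arm with more omissions. No calculation here shows a reversal. With equal timing accuracy the planned difference is about 0 s, so the demonstrated risk is a hidden difference.

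It can be argued that an event seen on video not to have happened is an observed omission and not missing data, so the complete-case rule need not apply. That is fair: the plan is silent and does not expressly exclude such teams. But the outcome as defined still yields no value, and nothing in the plan supplies one.

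Other outcomes do not fill the gap. Section 7.4.3 covers first events, other drugs and CPR quality. Section 7.4.4 covers dose deviation and does not define omission. Section 6.1 mentions compliance with AHA targets but ties no analysis to it.

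Finally, the stakes are limited. The omission rates are assumed, pulse checks and shocks have more due events than epinephrine and so lose a smaller share when the last is omitted, and these repeat-interval outcomes are not itemised in section 4. All of this stands and limits the weight of the point.

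**Conclusion.** The concern holds for omissions with no later event. The outcome in 7.4.5 penalises a skipped event that is followed by another and ignores one that is not. For epinephrine with a first dose at 165 s, the ignored excess is 75 s when the last dose is omitted and 315 s when every repeat is omitted. These figures follow from the plan's own window, target and typical first-dose time.

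The effect on the arm comparison depends on assumed omission rates, so the simulated differences show what could be concealed and do not predict it. If omission is equal between arms, no bias of this kind appears. The point concerns a secondary outcome and leaves the primary analysis untouched. It should be settled before data are unlocked, because a rule chosen after seeing omissions by arm would be data-driven.

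**What to change.** Amend 7.4.5 before data are unlocked, keeping the planned mixed model:

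1. Treat the last interval as open until the scripted end of the scenario (epinephrine, pulse checks) or of the shockable phases (shocks). When elapsed time exceeds the plan's own target, enter the excess in the model as that interval's minimum deviation.
2. State how many events are due per scenario under the plan's targets, and report by arm the number omitted.
3. Report by arm the number of teams with no scorable interval. Item 1 does not give every team a value. A team with no first event has no starting point, and one whose only epinephrine dose comes after 720 - 240 = 480 s has neither a closed interval nor an excess.

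The cost is a short SAP amendment and a few lines of code, using event times from the session video. The small downside is that an open-interval value is a lower bound on the true deviation, which the report should state.

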#### **7.4.6 Secondary outcomes - UEQ and TAM (for intervention group only)**

The User Experience Questionnaire (UEQ) and the Technology Acceptance Model (TAM) survey will be administered to participants in the InterFACE-AR group only. Rather than presenting data for each individual item, we will report the statistical summaries (mean and standard deviation) for each construct within both tools. The UEQ includes six constructs: attractiveness, perspicuity, efficiency, dependability, stimulation, and novelty. The TAM includes two constructs: perceived usefulness and perceived ease of use. For each construct, the mean and standard deviation will be reported, and Cronbach's alpha will be calculated to assess the internal consistency of the items within each construct.

In the case of missing data, a complete case analysis will be conducted. No multiple imputations are planned. All statistical tests will be two-sided with a type one error risk of 5%. All statistical analyses will be performed with R software (version 4.5.0; Foundation for Statistical Computing).

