## **2.7 Criteria for Discontinuing or Modifying Interventions**

We do not anticipate modification or discontinuation of the allocated simulation condition for trial participants. Each session will follow the planned protocol for a full 60-minute scenario per participant, scheduled several weeks in advance to ensure availability of the participants without repercussions on their normal duty. All participants will have prior authorization from their hierarchy to attend. As a simulation study with high-fidelity manikins and no patient involvement, the intervention is highly feasible and carries minimal risk. Only in exceptional circumstances such as an unforeseen technical failure of the simulator/AR device or a participant-initiated request may the session be briefly paused or, if necessary, terminated and reported.

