### **6.2 Retention and Follow-up**

All activities occur in a single, same-day session. No post-session follow-up is planned. Retention is promoted by scheduling sessions several weeks in advance with managerial approval, issuing confirmation/reminder notices, and on-site check-in to minimize delays. Attendance is logged, and brief rescheduling windows are available on the day if needed.

If a participant discontinues or deviates from the assigned condition, we will record: allocation, reason/timing of discontinuation/deviation, and all outcome data available up to that **point**. These data will be included in the intention-to-treat dataset. No additional outcome collection after the session will occur.

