## **7. Statistical considerations**

### **7.1 Power and Sample Size Calculation**

The calculation is based on the primary outcome, time to first epinephrine dose. Prior data report a median of approximately 165 seconds (IQR of 139 to 173 seconds). Using the Greco et al. approach, and using the 1st and 3rd quartiles, we estimate SD as  $(173-139)/1.35 = 25.2$  seconds. With a two-sided

$\alpha=.05$  and 90% power to detect a clinically meaningful absolute reduction of 35 seconds, and assuming similar variability between groups, 18 teams (9 per arm) are required.

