#### 7.4.4 Secondary Outcomes – Medication dose deviations

Medication dose deviations are defined as 10% deviated from the guideline dosage. Epinephrine, amiodarone and calcium doses will be examined and measured as dichotomous outcomes. They will be presented as counts and percentages for each study arm. Odds ratios will be calculated to assess the relative effect of the intervention. To address small cell counts, the Haldane–Anscombe correction will be applied. Risk differences (RD) will also be calculated to assess the absolute effect of the intervention, with 95% confidence intervals estimated using Newcombe’s method. Fisher’s exact test will be used to calculate p-values. A template table is presented below.

|                                        | InterFACE-AR | PALS cards | Odds ratio
(95% CI)* | Risk difference
(95% CI)** | P
value*** |
|----------------------------------------|--------------|------------|-------------------------|-------------------------------|---------------|
| Epinephrine dose deviation >10%, n (%) | X (X%)       | X (X%)     | X (X, X)                | X (X, X)                      | X             |
| Amiodarone dose deviation >10%, n (%)  | X (X%)       | X (X%)     | X (X, X)                | X (X, X)                      | X             |
| Calcium dose deviation >10%, n (%)     | X (X%)       | X (X%)     | X (X, X)                | X (X, X)                      | X             |

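### No value is set for a task never completed within the scenario, so complete-case analysis can bias the late secondary times

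*Combined protocol and SAP*

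**What the plan says.** The scenario in Section 3.2 is fixed in length ("A 12-minute CA simulation scenario"): three four-minute rhythms, then return of circulation. The first shockable rhythm appears at 4 minutes. Section 4 defines the primary outcome as seconds to a completed epinephrine injection. Sections 7.4.2 and 7.4.3 analyse this and the other task times by a mean or median difference, with a bootstrap interval and a permutation p-value.

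The only missing-data text closes Section 7.4.6: "In the case of missing data, a complete case analysis will be conducted", followed by "No multiple imputations are planned". It stands under the questionnaire heading, but the next sentences set the significance level for all tests and the software for all analyses, so it reads as trial-wide. The SPIRIT checklist marks sensitivity analyses (item 27d) as not applicable.

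Two other passages bear on losses. Section 2.7 allows a session to be paused or ended: "Only in exceptional circumstances such as an unforeseen technical failure of the simulator/AR device", or at a participant's request. Section 6.2 keeps outcome data recorded up to a discontinuation: "These data will be included in the intention-to-treat dataset".

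For doses, Section 7.4.4 says "Epinephrine, amiodarone and calcium doses will be examined and measured as dichotomous outcomes". It gives no denominator and no coding for a drug never given.

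**The concern.** A team that never performs a task has no time to abstract from the video. The plan assigns it no value, so complete case is the only rule left to apply, and the team drops out of that comparison. Not doing the task is the worst result on a timing outcome, and it arises after randomisation. If it is more common in one arm, the analysis compares only the successful teams, and the groups compared are no longer the randomised ones. The tool is meant to improve guideline adherence, so a difference between arms in omissions is plausible. With nine teams per arm, each exclusion counts.

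**Working it through.** **Inputs.** From the documents: 9 teams per arm, 35 s target effect, median 165 s and IQR 139 to 173 s for the primary outcome (Section 7.1); scenario of 12 × 60 = 720 s (Section 3.2). Section 2.7 mentions a 60-minute scenario, which I read as the whole session. Assumed, because the documents are silent: non-completion rates and the distributions of the late secondary times.

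**1. The plan's own figures.** SD = (173 − 139)/1.35 = 25.2 s, as stated. The sample size does not reproduce: 2 × (1.960 + 1.282)² × 25.2²/35² = 10.9, so 11 per arm for the stated "90% power to detect a clinically meaningful absolute reduction of 35 seconds". Nine per arm gives 79.0% power (t) or 83.8% (normal). That is a separate matter, and nothing below depends on it.

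**2. Primary outcome.** (720 − 165)/25.2 = 22.0 SD. On these inputs non-completion is effectively nil, and simulated complete case returns -35.0 s, so there is no bias. If the slowest 1, 2 or 3 control teams were nonetheless lost, the simulated estimate would shrink to -30.5, -26.1 or -22.8 s, and t-test power would fall from 79% to 69%, 56% or 43%.

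**3. A late task with a plain shift (assumed normal, SD 120 s, true effect -60 s).** With z = (720 − μ)/120, the proportion not finishing is 1 − Φ(z), and the mean among finishers is μ − 120 φ(z)/Φ(z). For a control mean of 600 s:

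- Control: z = 1.0, 15.9% unfinished, finishers' mean 565.5 s.
- Intervention (mean 540 s): z = 1.5, 6.7% unfinished, finishers' mean 523.3 s.
- Difference: about -42 s.

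Simulation with 9 per arm gives:

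| Control mean (s) | Unfinished, control vs intervention | Complete case (s) | Capped at 720 s (s) | Wrong-sign estimates, complete case |
|---|---|---|---|---|
| 500 | 3.4% vs 1.0% | -53.9 | -58.9 | 16.0% |
| 600 | 15.9% vs 6.7% | -42.0 | -53.5 | 20.2% |
| 650 | 27.9% vs 14.0% | -35.2 | -47.8 | 23.7% |
| 700 | 43.4% vs 25.3% | -28.1 | -39.7 | 27.9% |

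With every latent time known, 14% of estimates have the wrong sign. The result is attenuation. A lognormal version (medians 600 and 480 s, sigma 0.6; 38% vs 25% unfinished) behaves the same way: -38.8 s by complete case against -65.2 s capped.

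**4. When the sign reverses.** Suppose six teams in each arm finish at 300, 330, 360, 390, 420 and 450 s. Three more intervention teams finish at 560, 620 and 680 s, and three control teams never finish.

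- Complete case: 4110/9 − 2250/6 = 456.7 − 375.0 = +81.7 s (medians 420 − 375 = +45 s), favouring control.
- Undone tasks at 720 s: 456.7 − 4410/9 = 456.7 − 490.0 = -33.3 s (medians 420 − 420 = 0 s).

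The permutation p-values for the means are 0.20 and 0.66. The direction of the estimate changes, but not the test decision.

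In a simulated mixture, one third of teams are weak and the tool makes them finish late instead of never. With 11%, 22% and 33% control non-completion and none in the intervention arm, complete case gives +16.6, +38.2 and +66.4 s, against -13.4, -26.3 and -39.9 s capped. With 22% in each arm the complete-case difference is -0.1 s, so there is no bias.

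**5. Sensitivity to an assigned maximum.** One team scored 720 s in an arm averaging 130 s moves that arm's mean by (720 − 130)/9 = 65.6 s; in an arm averaging 165 s, by (720 − 165)/9 = 61.7 s. Both exceed the 35 s target.

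**The case against.** The strongest reply is that the documents never say an undone task is coded as missing. That is true. The exclusion follows because no other rule exists. If the sentence in Section 7.4.6 is instead confined to the questionnaires, the time outcomes have no rule at all, which needs the same repair.

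Several stronger readings are tempting but unsupported:

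- *The primary result is compromised.* On the plan's own figures it is not (step 2).
- *Reversal is to be expected.* It needs unequal non-completion and a tool that turns omission into late completion. The airway role is also played by a scripted actor (Section 2.4), which may make airway omissions rarer.
- *Intervention teams stopped for device failure vanish altogether.* Section 6.2 keeps the times they have already recorded; only tasks not yet reached lack a value. Section 2.7 also covers simulator failure, which can occur in either arm.
- *Omitted drugs escape the error count.* Section 4 defines an error as more than 10% from the correct weight-based dose, and a zero dose deviates by 100%, so omission may already count. But errors are measured from residual syringe volume, and the coding where no syringe was prepared is unstated.

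A blanket 720 s for every missing time would also be unsafe. Applied to one intervention session stopped before epinephrine, it would move a -35 s mean effect to about -35 + 65.6 = +30.6 s. Whether a stopped session counts as worst performance is an estimand choice. Nor does 720 s fit every outcome: defibrillation timed from the first shockable rhythm has at most 720 − 240 = 480 s.

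**Conclusion.** The gap is real, and it concerns mainly the late or short-window secondary times: defibrillation, the first and second hyperkalemia drugs, and the definitive airway. As written, teams that complete the scenario without doing the task drop out, and the comparison conditions on success. The usual consequence is attenuation: in the assumed examples a true -60 s is estimated at between -54 and -28 s. Reversal is possible under the narrower conditions of step 4. Equal non-completion in the mixture model produced no bias. All these sizes rest on assumed rates and distributions, since the documents give none. The primary outcome is very unlikely to be touched, although it too lacks a rule. For dose deviations the finding is only that the denominator and the coding of an omitted drug are unstated.

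**What to change.** Add to Section 7.4, before the data are analysed:

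1. A task not done by the end of a completed scenario is an outcome, not missing data. The team stays in the analysis with the worst rank, or with the time from that outcome's own time zero to scenario end, in the same permutation test. State each secondary outcome's time zero; Section 4 gives one only for the primary.
2. Report the number of teams not completing each task, by arm.
3. Reserve complete case for technical loss: lost video, or a session stopped by simulator or device failure before the task was reached. Report these losses by arm, and keep times already recorded, as Section 6.2 provides. Score stopped sessions as the worst outcome only in a sensitivity analysis.
4. For dose deviations, use all randomised teams with a scenario as the denominator, and show drugs never given, by arm, as deviations or as a separate category.
5. Say that the missing-data rule covers all outcomes.

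The cost is a paragraph of SAP text and a few lines of code, with no new data collection. The downsides are ties at the maximum and a mean that depends on the assigned value (step 5). Where non-completion occurs, a rank or median summary is preferable: with nine teams the median is the fifth ordered value, so up to four non-completers in an arm leave it independent of the value assigned.
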